## Abstract

**Background:**

The prevalence of heavy drinking among college students and its associated health related consequences highlights an urgent need for alcohol prevention programs targeting 18 to 24 year olds. Nevertheless, current alcohol prevention programs in the Netherlands pay surprisingly little attention to the drinking patterns of this specific age group. The study described in this protocol will test the effectiveness of a web-based brief alcohol intervention that is aimed at reducing alcohol use among heavy drinking college students aged 18 to 24 years old.

**Methods/Design:**

The effectiveness of the What Do You Drink web-based brief alcohol intervention will be tested among 908 heavy drinking college students in a two-arm parallel group randomized controlled trial. Participants will be allocated at random to either the experimental (*N *= 454: web-based brief alcohol intervention) or control condition (*N *= 454: no intervention). The primary outcome measure will be the percentage of participants who drink within the normative limits of the Dutch National Health Council for low-risk drinking. These limits specify that, for heavy alcohol use, the mean consumption cannot exceed 14 or 21 glasses of standard alcohol units per week for females and males, respectively, while for binge drinking, the consumption cannot exceed five or more glasses of standard alcohol units on one drinking occasion at least once per week within one month and six months after the intervention. Reductions in mean weekly alcohol consumption and frequency of binge drinking are also primary outcome measures. Weekly Ecological Momentary Assessment will measure alcohol-related cognitions, that is, attitudes, self-efficacy, subjective norms and alcohol expectancies, which will be included as the secondary outcome measures.

**Discussion:**

This study protocol describes the two-arm parallel group randomized controlled trial developed to evaluate the effectiveness of a web-based brief alcohol intervention. We expect a reduction of mean weekly alcohol consumption and frequency of binge drinking in the experimental condition compared to the control condition as a direct result of the intervention. If the website is effective, it will be implemented in alcohol prevention initiatives, which will facilitate the implementation of the protocol.

**Trial registration:**

Netherlands Trial Register NTR2665.

## Background

The prevalence of heavy alcohol use among young adults and its associated health related consequences has become a great public health concern in most Western countries [1]. The percentage of heavy drinkers is particularly high among college students [2-5] and those who are affiliated with fraternities and sororities [6-8]. In the Netherlands, a substantial number of young adults engages in heavy alcohol use [3]. Heavy alcohol use can have detrimental short and long-term health related consequences for young adults, including risky sexual behaviour [9], brain damage [10], problematic alcohol use in adulthood [11], liver damage [12], and various types of cancer [1]. Heavy drinking among young adults and its social and economic burden highlights an urgent need to develop alcohol prevention programs targeted at 18 to 24 year olds. Nevertheless, current alcohol prevention programs in the Netherlands pay surprisingly little attention to young adults' drinking patterns. The study described in this protocol will test the effectiveness of a web-based brief alcohol intervention aimed at reducing alcohol use among heavy drinking college students aged 18 to 24 years old.

Previous studies have found that web-based brief alcohol interventions or individual single-session interventions without therapeutic guidance can be effective in reducing heavy alcohol use among young adults and students [13-19]. Originally, brief alcohol interventions were delivered using conventional methods, such as face-to-face [20,21] and postal mail methods [22]. Recently, interventions have been delivered electronically via computer programs [17] and Internet [16,23]. This web-based approach may have a number of advantages over the more traditional delivery methods. First, heavy drinkers are generally not interested in any type of treatment because they either do not think of themselves as heavy drinkers or they do not recognize that their drinking patterns may cause serious health risks; therefore, they use interventions without therapeutic involvement rather than group and individual counselling treatments to address their drinking behaviour [13]. Second, web-based brief alcohol interventions allow easy access to large audiences. Third, such interventions allow participants to access the intervention at their own convenience, which may enhance participants' feelings of privacy and anonymity. Fourth, these types of interventions are brief; therefore, less time-consuming and easier to implement. Finally, tailored information can be provided in an automated, cost-effective and flexible way [24]. Therefore, web-based brief alcohol interventions may be particularly suitable for our target population, especially considering that the majority of young adults in Western countries have access to the Internet and make frequent use of Internet technologies [25,26].

### Objectives and hypotheses

The objective of our study is to assess the effectiveness of the web-based brief alcohol intervention What Do You Drink (WDYD) among heavy drinking college students aged 18 to 24 years old. The effectiveness of the intervention will be tested at one month and six months after the intervention. In total, five pre-tests and 26 post-tests will be assessed weekly using Ecological Momentary Assessment (EMA) [27]. We expect that a larger percentage of participants in the intervention condition will drink within the normative limits of the Dutch National Health Council for low-risk drinking [28] compared to the control condition as a direct result of the intervention. This means that their consumption will not exceed a mean heavy alcohol use consumption of more than 14 or 21 glasses of standard alcohol units per week for females and males, respectively and/or, in case of binge drinking, five or more glasses of standard alcohol units on one drinking occasion at least once per week within one month and six months after the intervention. One standard alcohol unit contains ten grams of ethanol. Moreover, it is hypothesized that participants in both arms of the intervention would reduce their mean weekly alcohol consumption and frequency of binge drinking; although, it is expected that the exposure to the WDYD web-based brief alcohol intervention will be more effective compared to no intervention.

## Methods/Design

### Trial design

The effectiveness of the web-based brief alcohol intervention for heavy drinking college students will be tested in a two-arm parallel group randomized controlled trial. Participants will comprise 908 heavy drinking college students aged 18 to 24 years old. They will be randomly assigned to either the experimental (*N *= 454: web-based brief alcohol intervention) or control condition (*N *= 454: no intervention).

### Participants

A convenience sampling strategy will be used to recruit participants from Higher Professional Education (HBO) Institutions and Universities in the Netherlands. We will recruit participants by distributing flyers at the HBO Institutions and Universities and sending e-mails with information about the study to college students. Respondents will be given an e-mail address to obtain additional information about the study. Then, they will be invited to complete an online screening questionnaire to establish whether they fulfil the inclusion criteria. The online screening questionnaire contains items on demographic characteristics, alcohol use, and willingness to change drinking behaviour. To fulfil the inclusion criteria participants have to: 1) be between 18 and 24 years old, 2) report heavy drinking in the past six months, 3) be willing to change alcohol consumption, 4) have access to the Internet, and 5) sign an informed consent. Heavy drinking is defined based on the above-mentioned definition of heavy alcohol use and binge drinking, and it differs across participants' sex. Participants should be either heavy alcohol users and/or binge drinkers to fulfil the inclusion criteria. College students showing symptoms of alcohol abuse or dependence, that is an AUDIT score of 20 or above [29], and/or receiving treatment for alcohol-related problems, will be excluded from the sample. Participants satisfying the inclusion criteria will be invited by e-mail to electronically sign the informed consent containing information about confidentiality, voluntary participation, and human subject protections. Approval for the design and data collection was already obtained from the Ethical Committee (ECG) of the Faculty of Social Sciences of Radboud University Nijmegen in the Netherlands.

### Interventions

The web-based brief alcohol intervention, What Do You Drink (WDYD), aims to detect and reduce heavy drinking of young adults who are willing to decrease their alcohol consumption, preferably below the Dutch guidelines for low-risk drinking. The intervention is based on Motivational Interviewing [30] and parts of the I-Change model [31] and focuses predominantly on the action phase of the behaviour change process. Knowledge, social norms, and self-efficacy are embedded as the most changeable determinants of behaviour change ([name], [name], [name], [name]: The development of a web-based brief alcohol intervention in reducing heavy drinking among college students: An Intervention Mapping approach, submitted).

The theoretical underpinning of web-based brief alcohol interventions is based on the literature on Motivational Interviewing [30] and social influence [32]. Motivational Interviewing, "a client-centred, directive method for enhancing intrinsic motivation to change by exploring and resolving ambivalence" [30], includes goal setting and action planning components [33]. A basic element in these types of interventions is the presentation of discrepant personal information to increase an individual's motivation to change or modify his or her behaviour [23]. A web-based brief alcohol intervention could present this discrepancy in two parts: a screening procedure and personalized feedback that is based on the screening outcomes. Topics that are addressed in the screening and the personalized feedback include personal drinking profile, risk factors, and normative comparisons. The inclusion of normative feedback is based on theory about social influence [32]. This type of feedback offers comparative information about personal drinking levels and drinking levels of a relevant comparison group, such as same-sex peers [23]. The use of personalized feedback implies that the intervention is "tailored" to the individuals' personal situation. Tailored interventions might be more effective than general interventions because the receiver of the intervention identifies him or herself with the personal-related information and pays more attention to the message and because they contain more relevant and less redundant information compared to general interventions [34].

The first part of WDYD focuses on the motivation phase of the behaviour change process and contains a homepage and a screening test with personalized feedback. The principle of a screening procedure with personalized feedback on alcohol-related knowledge and social norms has been shown effective when used in web-based brief alcohol interventions [15,16,19,35]. The screening test includes items addressing participants' name, sex, age, education level, weight, alcohol use, willingness to change alcohol consumption, average expenses on consumed alcohol beverages, and descriptive social norms. After completing the screening test, participants will receive personalized feedback that will depend on their answers to the questions on the screening test. The feedback will be tailored to participants' sex, alcohol intake, and perceived social norm. It will provide 1) advice about drinking according to the guidelines of the Dutch National Health Council, recommending that men should not drink more than two glasses alcohol per day and women one glass alcohol per day [28]. Further, it will provide information about 2) the amount of glasses of standard alcohol units that the participant consumed in the last year, with estimates of the number of calories consumed, the amount of weight added because of drinking, and the amount of money spent on drinking. Lastly, it will depict 3) a bar chart comparing the number of glasses of standard alcohol units per week that participants think their same-sex peers consume with the number of glasses of standard alcohol units per week that participants' same-sex peers actually consume. The comparative data of the descriptive social norms from a proximal reference group will be retrieved from alcohol prevalence estimates for the same-sex groups found in a nationally representative sample of the general population [36]. After receiving personalized feedback, participants will be offered access to the second part of the intervention via a registration and sign-up procedure.

The second part of WDYD focuses on the action phase of the behaviour change process, with a general goal of reducing heavy drinking. Specific proximal (short-term) goals, also called action plans, are found to be more effective compared to distal (long-term) goals [33]. Therefore, participants will be prompted to make decisions about the maximum amount of glasses of standard alcohol units they want to drink on every day of the week at a given point of time, preferably within the limits of low-risk drinking.

In addition to goal setting and action planning, the WDYD intervention will include self-efficacy. A substantial number of studies have indicated that adolescents with low self-efficacy for avoiding heavy drinking in social situations are more likely to engage in heavy drinking [37-39]. Therefore, WDYD focuses on strengthening participants' drinking refusal self-efficacy [40] by proving tips to resist alcohol in different drinking situations, which is expected to lead to behavioural change to succeed and maintain drinking goals. Participants will be asked to choose three out of the twelve provided drinking situations (derived from the Young's drinking refusal self-efficacy questionnaire (DRSEQ-RA: [38,41])). Subsequently, participants will be asked to give a rationale why they find it hard to resist alcohol in the three chosen drinking situations.

Finally, several tips will be offered for each of the chosen drinking situations to help participants cope with these situations in order to succeed and maintain general and specific drinking goals.

### Intervention conditions

Participants will be randomly assigned to either the experimental condition - exposure to the WDYD intervention - or the control condition - no intervention.

### Data collection

An overview of measurements is given in Figure 1. The baseline assessment and pre-tests (one month before the intervention) are already collected in January 2011. The post-tests data will be obtained from weekly EMA measurements collected over 26 fixed time points following the intervention, that is, from February until August 2011, with a final follow-up in November 2011. Every Monday, participants will report 1) the number of glasses of standard alcohol units they drank during each day of that week, 2) the frequency of binge drinking within that week, and 3) the frequency of drinking and their ability to resist 26 different drinking situations during that week. Attitudes, self-efficacy, subjective norms and alcohol expectancies will be measured at baseline, immediately after the intervention, and one and six months after the intervention. In addition, a cost-effectiveness evaluation will be conducted along with the RCT, with follow-ups at baseline and one and six months. After completing the final follow-up, all participants will receive a monetary reward of hundred euro.

**Figure 1 F1:**
[figure not shown]
**Study design**.

### Outcomes

The primary outcome measure will be the percentage of participants who drink within the normative limits of the Dutch National Health Council for low-risk drinking. Thereby, their mean consumption rate cannot exceed 14 or 21 glasses of standard alcohol units per week for females and males, respectively, and/or five or more glasses of standard alcohol units on one drinking occasion at least once per week within one month and six months after the intervention. In addition, reductions in mean weekly alcohol consumption and frequency of binge drinking will also be included as primary outcome measures.

Weekly alcohol consumption will be measured with the Dutch version of the Alcohol Weekly Recall [42]. Respondents will be asked to indicate retrospectively how many glasses of standard alcohol units they consumed in the last seven days. To ensure standardized responses, an overview of standard units for various beverages will be provided. The frequency of binge drinking will be measured by asking respondents how often they consumed five or more glasses of standard alcohol units on one drinking occasion at least once per week in the past week. They will be asked to respond on a 7-point scale ranging from (1) "never" to (7) "every day".

Weekly EMA will be employed in the pre-tests and post-tests to assess the secondary outcome measures. EMA is a generic term encompassing various research methods that utilize repeated measurements to assess people's current or very recent states or behaviours in their natural environments according to strategically selected moments in time [27]. One of the advantages of EMA is that it contains measures that are ecologically more valid, as data are collected in real-world environments. The most relevant advantage of EMA is that it reduces bias due to memory effects because it assesses the participants' most recent alcohol use instead of asking them to recall their past alcohol consumption. This enhances the validity of self-reports [43]. Scholars who have employed EMA using different designs showed that EMA is a useful methodology for assessing drinking patterns [44].

### Sample size

The sample size for our study will be based on a power calculation for detecting an increase in the percentage of participants showing low-risk drinking (i.e., who do not show heavy drinking) after one month of 42% in the experimental group versus 31% in the control group (Boon B, Risselada A, Huiberts A, Smit F: Reduced alcohol consumption in male adults due to a one time computer tailored advice: A randomised controlled trial, in press). When using a 2-sided test at alpha = 0.05, a power of (1-beta) = 0.80, and expecting a worst case scenario of 30% loss-to-follow-up after randomization, we will need a total sample size of 908 respondents (*N *= 454 per condition).

### Randomization

An independent researcher of the Behavioural Science Institute will randomly assign participants to the experimental and the control condition before baseline assessment. Randomization will be carried out centrally using a blocked randomization scheme (block size 4), and it will be stratified by sex and education level, as the Dutch guidelines for low-risk drinking differ for men and women.

### Statistical methods

To test the effectiveness of the web-based brief alcohol intervention, significantly more participants in the experimental condition would need to fulfil the criteria for low-risk drinking at one and six months follow-up compared to participants in the control condition; therefore, we will employ binomial statistical analyses to assess differences between the control and experimental conditions. Logistic regression models in SPSS and/or Mplus will be analyzed to test how the intervention relates to aggregated measures of drinking one month, three months, and six months after the intervention as well as at the final follow-up. The effect sizes as well as confidence intervals will be reported to determine both the magnitude and effect of the web-based brief alcohol intervention on heavy drinking. In addition, we will test whether age, sex, and drinking status moderate the main effect of the intervention on heavy drinking. We are also interested in possible mediators in the relation between the web-based brief alcohol intervention and alcohol consumption. Using SPSS and/or Mplus, we will test whether attitudes, social norms, and self-efficacy (ASE-model) could mediate the main effect because WDYD focuses predominantly on the latter two alcohol-related cognitions. The EMA data will comprise a large number of observations for each participant, making it possible to examine alcohol use of each participant over time. Therefore, in addition to the binomial statistical analyses, we will examine the effect of the intervention on trajectories and growth curves of alcohol consumption [45]. The EMA enables us to examine specific point in time at which the intervention is most successful and its effect size starts decreasing. Further, HLM survival analyses will be conducted to test the efficacy of the intervention. Moreover, a cost-effectiveness evaluation will be carried out.

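### The methods named for the follow-up time points are binomial and logistic, which do not fit two of the three primary outcomes: mean weekly consumption and binge-drinking frequency

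*Protocol article*

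**What the plan says.** The Outcomes section of the protocol article sets three primary outcomes.

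- **Low-risk drinking (binary):** "The primary outcome measure will be the percentage of participants who drink within the normative limits of the Dutch National Health Council".
- **Mean weekly consumption and binge frequency (quantitative):** "reductions in mean weekly alcohol consumption and frequency of binge drinking will also be included as primary outcome measures".

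The same section fixes the scales of the last two. Weekly consumption comes from a recall instrument that asks "how many glasses of standard alcohol units they consumed in the last seven days". Binge frequency is a single item with seven ordered response categories, running from never to every day.

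Objectives and hypotheses sets the effectiveness tests at one and six months. It expects that both arms "would reduce their mean weekly alcohol consumption and frequency of binge drinking", with a larger effect under the intervention.

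Statistical methods links success to the low-risk criterion at one and six months and concludes that "we will employ binomial statistical analyses to assess differences between the control and experimental conditions". It continues: "Logistic regression models in SPSS and/or Mplus will be analyzed to test how the intervention relates to aggregated measures of drinking", at "one month, three months, and six months after the intervention as well as at the final follow-up". As a supplement to the binomial analyses, it then plans to examine the intervention effect on growth curves of alcohol consumption from the weekly data. It also lists survival analyses without naming an event or outcome.

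**The concern.** Two primary outcomes are a mean and an ordered score, while the methods named for the follow-up time points are built for yes/no data. An ordinary logistic model needs a binary response. To apply it to average glasses per week or to the binge item, the analyst must choose a cut-off, and the article gives none apart from the low-risk limits. Using those limits would largely repeat the first primary outcome.

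What is at stake is whether the trial can report, at its own primary time points, the effect that its hypotheses describe: a greater reduction in mean weekly consumption and in binge frequency. An odds ratio from a dichotomised measure does not answer that question. Dichotomising also discards information, and a cut-off chosen after the data are seen would leave room for selection.

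**Working it through.** **Outcome against method**

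| Primary outcome | Scale in the article | Method named for one and six months | Other named analysis |
|---|---|---|---|
| Low-risk drinking | Binary | Binomial, logistic: fits | None needed |
| Mean weekly consumption | Glasses in seven days | Logistic on aggregated measures: no estimate of a mean difference | Growth curves by condition; no one- or six-month contrast stated |
| Binge frequency | Seven ordered categories | Logistic on aggregated measures: needs a cut-off if binary | None expressly tied to it |

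The survival analyses fill no cell, because no event is named for them.

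**The plan's own sample size**

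Inputs from the Sample size section: 42% v 31%, two-sided alpha 0.05, power 0.80, 30% loss to follow-up, total 908.

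- Mean proportion: (0.42 + 0.31)/2 = 0.365.
- Without continuity correction: n = [1.960 × √(2 × 0.365 × 0.635) + 0.8416 × √(0.42 × 0.58 + 0.31 × 0.69)]² / 0.11² = (1.334 + 0.569)² / 0.0121, about 300 per arm.
- With continuity correction: n′ = (n/4) × [1 + √(1 + 4/(n × 0.11))]², about 318 per arm.
- Allowing for loss: 318/0.70 = 454.3, so 454 per arm and 908 in total. The stated figure is reproduced. It is sized on the binary outcome only.

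**Illustration of what a cut-off costs**

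The documents give no standard deviation and no expected difference for glasses per week or for the binge item, so power for those outcomes cannot be derived. The following assumes one normal latent drinking measure, equal SDs in both arms and a single cut-off.

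- Shift that gives 42% v 31%: d = Φ⁻¹(0.42) − Φ⁻¹(0.31) = −0.202 + 0.496 = 0.294 SD.
- Per arm for 80% power on means: 2 × (2.8016/0.294)², about 182.
- Per arm for 80% power on the dichotomy, also without continuity correction: about 300.
- Information kept: 182/300 = 0.61.
- With 318 analysed per arm, power is about 82% for the dichotomy (uncorrected test) and about 96% for means.

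The comparison must be 182 against 300. Setting 182 against 318 would mix an uncorrected with a corrected figure and overstate the gap.

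**The case against.** **Consumption is not left untested.** A reader might infer that both quantitative outcomes are either dichotomised or never tested. For weekly consumption the article does not support that. It plans growth curves of alcohol consumption by condition with no cut-off, and it says the weekly data allow a look at when the effect is greatest and when it starts to fade. This part of the objection stands. What remains is that the growth curves are additional, and that no contrast at one or six months is stated.

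**Logistic could mean ordinal.** The binge item is ordered, and the article does not say that the logistic models are binary. An ordinal logistic model would suit the item. The text makes this reading unlikely, because the growth curves are introduced as a supplement to analyses described as binomial. It is not excluded, and if it was intended, saying so settles that part.

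**The logistic sentence may concern low-risk status only.** The sentences around it deal with the low-risk criterion and heavy drinking. On that reading the model is sound, but the two other primary outcomes then have no comparison named for the follow-up time points.

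**A condensed article may leave models to an analysis plan.** That is true, and a missing model alone would be no finding. Here, however, the article does name methods and time points, and as written those methods do not fit the stated scales.

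**The power figures are borrowed.** This stands. The 42% v 31% effect belongs to low-risk drinking, which combines sex-specific weekly limits with a binge criterion and is not one cut on one variable. The figures show the general price of a cut-off, not the loss on either outcome.

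**Conclusion.** The point holds in a limited form. At one and six months, the methods that the article names do not estimate a difference in mean weekly glasses, and they do not use the full binge scale without a cut-off. Consumption is analysed without a cut-off only through supplementary growth curves. Binge frequency has no analysis expressly tied to it. This should be corrected, but it does not undermine the design.

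The size is illustrative: about 61% of the information is kept by a single cut, on a latent shift of about 0.29 SD. It rests on approximate normality, equal SDs and one common cut-off, none of which the documents establish for these outcomes. A reader might infer that the sample size is wrong. It is not challenged: 908 is reproduced for the binary outcome on which it is based.

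**What to change.** In Statistical methods, make three statements.

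1. Binomial and logistic analysis applies to low-risk drinking only.
2. Mean weekly glasses are compared between arms at one and six months, with a 95% confidence interval. Use a linear model on a suitable scale, a negative binomial model, or a contrast taken from the growth model already planned.
3. Binge frequency is compared at the same time points with an ordinal model of the seven-category item, with a 95% confidence interval. A count-of-days model does not match the item: zero to seven days would need eight values, and the scale has seven categories.

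The other growth-curve analyses can stay as supporting work. The cost is a change of wording and two standard models, or one such model plus contrasts from the growth model, on data the plan already collects. No participants or visits are added.

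### The plan presumes that the weekly data contain a peak effect and a later decline; a peak chosen from the data is overstated, and the decline after it can be created or exaggerated by selection

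*Protocol article*

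**What the plan says.** The Data collection section provides "weekly EMA measurements collected over 26 fixed time points following the intervention". Under Statistical methods the main approach is a comparison of low-risk drinking at one and six months. Logistic models of aggregated drinking at one, three and six months and at the final follow-up come with it. The weekly data then receive a further analysis: "in addition to the binomial statistical analyses, we will examine the effect of the intervention on trajectories and growth curves of alcohol consumption".

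A statement on timing follows directly: "The EMA enables us to examine specific point in time at which the intervention is most successful and its effect size starts decreasing".

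No rule is given for finding that point. The text does not first ask whether the arm difference changes over time, gives no interval for the location of the peak, and does not label the result exploratory. The confirmatory time points are fixed elsewhere: "The effectiveness of the intervention will be tested at one month and six months after the intervention" (Objectives and hypotheses).

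**The concern.** The two quantities named, the time of greatest success and the start of the decrease, are both chosen by looking at the data. The maximum of a set of noisy estimates exceeds the true effect on average, because the week or curve position that wins is partly the one with favourable error. Values after a selected maximum are then lower on average even if the true effect never moves.

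The sentence takes the existence of a peak and a decline as given, so nothing in the stated aim allows the answer that the effect did not change detectably over the 26 weeks. At stake are three possible statements in the trial report: when the intervention works best, how large the effect is at that time, and when it begins to wear off.

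**Working it through.** **Inputs from the protocol (Sample size).** Low-risk drinking "after one month of 42% in the experimental group versus 31% in the control group"; "When using a 2-sided test at alpha = 0.05, a power of (1-beta) = 0.80"; "expecting a worst case scenario of 30% loss-to-follow-up after randomization"; "we will need a total sample size of 908 respondents", that is 454 per arm. The number of weekly points is 26 (Data collection).

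**Reproducing the plan's own figure.** The mean rate is (0.42 + 0.31)/2 = 0.365.

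- n = [1.96·√(2·0.365·0.635) + 0.842·√(0.42·0.58 + 0.31·0.69)]² / 0.11² = 299.5 per arm.
- With continuity correction: n/4·[1 + √(1 + 4/(n·0.11))]² = 317.4, so 318 per arm.
- Allowing for 30% loss: 318/0.70 = 454.3 per arm. This is 908 in total if rounded to the nearest whole number, or 910 if rounded up. The stated 908 reproduces.

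**Precision of one weekly contrast.** With 318 evaluable per arm and a weekly low-risk rate near 36.5% (an assumption, since the protocol gives rates only at one month), SE = √(2·0.365·0.635/318) = 0.038, or 3.8 points.

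**Simulation with a constant true effect.** Each setting used 100,000 draws of 26 correlated weekly estimates. The correlation between weekly estimates is not in the protocol, so it is an assumption and is varied. Overstatement is the mean of the selected maximum minus the true effect. The quadratic was fitted to the 26 weekly arm differences by unweighted least squares.

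| Assumed correlation | Best raw week, in SE | Best raw week, in points | Quadratic peak, in points | Quadratic peaks before week 26 |
|---|---|---|---|---|
| Exchangeable 0.9 | 0.63 | 2.4 | 0.5 | 70% |
| Exchangeable 0.7 | 1.09 | 4.2 | 0.9 | 71% |
| Exchangeable 0.5 | 1.40 | 5.3 | 1.1 | 71% |
| Exchangeable 0.3 | 1.66 | 6.3 | 1.3 | 71% |
| Autoregressive 0.8 | 1.56 | 6.0 | 3.2 | 70% |
| Autoregressive 0.7 | 1.72 | 6.6 | 3.0 | 70% |
| Autoregressive 0.5 | 1.86 | 7.1 | 2.5 | 71% |
| Autoregressive 0.3 | 1.94 | 7.4 | 2.1 | 71% |

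Weighting the quadratic fit by the assumed correlation lowers its autoregressive figures slightly, to between 2.0 and 2.9 points. In about 40% of runs the quadratic has its maximum strictly inside the 26 weeks. In roughly another 30% the maximum is at week 1. Both would be read as a peak followed by a decline. The best raw week falls before week 26 in 94% to 96% of these runs. With no effect at all, some raw week reaches nominal significance in 17% (exchangeable 0.9) to 72% (autoregressive 0.3) of runs.

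**If the effect truly wanes.** Assume 11 points in week 1, decaying exponentially with a time constant of 13 weeks. The best raw week then shows on average 13.1 points (exchangeable 0.5) or 12.3 points (exchangeable 0.7). The true effect at the chosen week averages 9.6 and 10.0 points. The correct week is chosen in 34% and 41% of runs. The peak is inflated, but most of the decline is real.

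**Effect of a prior global test.** With a constant effect, requiring a significant 5% test of the linear and quadratic arm-by-time terms (correlation treated as known) leaves about 5% of runs in which any change could be described. About 3.5% would show a peak before week 26.

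**The case against.** The strongest reply is that the protocol does not describe a search of 26 weekly contrasts. The statement on timing follows the growth-curve sentence and most naturally continues it. This stands, and it means that the raw-week figures are an upper reading. A reader might infer that the plan commits to picking the best week and will overstate the effect by 4 to 7 points; the text does not support that. The growth-curve reading makes the bias smaller without removing it, and the false decline remains frequent.

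A reader might also infer that any reported decline would be an artefact. That requires a constant true effect. A single-session intervention may well wane, and selection then mainly inflates the peak.

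It can be said that the timing result would govern when further contact is offered to participants. The protocol mentions no such use. It speaks only of implementing the intervention if it proves effective, and effectiveness is judged at time points fixed in advance.

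The percentage-point scale is borrowed from the binary outcome, while the growth curves concern alcohol consumption. That is fair, so the results in SE units carry over more safely than those in points.

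Finally, an interaction test, bands and intervals are details that a condensed article may leave to an analysis plan. Their absence alone would be no finding. What the article does fix is an aim that presumes a peak and a decline, and that aim needs rewording whatever the analysis plan contains.

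**Conclusion.** The point holds as a limited one about a secondary analysis. The stated aim presumes a peak and a decline, and any peak chosen from the data will be overstated. With a constant true effect the overstatement is about 0.5 to 3 points on a fitted quadratic curve and about 2.4 to 7.4 points for the best raw week, against a planned difference of 11. On either reading an apparent decline is the usual result: about 70% of runs for the quadratic and more than 90% for the raw maximum.

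These sizes depend on three assumptions: 318 evaluable per arm each week, a weekly low-risk rate near 36.5%, and between-week correlations from exchangeable 0.9 to autoregressive 0.3. The direction of the bias does not depend on them. The sample size and the primary comparisons at one and six months are not affected.

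**What to change.** Within the growth-curve analysis already planned:

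1. Prespecify one smooth arm-by-time function over the 26 weeks. Avoid straight pieces between knots, because such a curve can peak only at a knot or an end.
2. Prespecify one global test of whether the arm difference changes over the 26 weeks. Describe a peak or an onset of decline only if that test is significant, and label the description exploratory.
3. Report the whole arm-difference curve with simultaneous 95% bands computed for the fitted model, and an interval for the location of the peak. Critical values derived for 26 separate weekly contrasts (about 2.8 to 3.1 at the correlations from 0.3 to 0.7) do not apply to a smooth curve, for which the value is smaller.
4. Take effect sizes from the time points fixed in advance (one, three and six months) and not from the selected peak. The global test limits false claims to about 5%, but it does not remove the overstatement in a peak that passes it.

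The timing sentence could be reworded to say that the trial will examine whether the effect changes over the 26 weeks and, if so, describe when. The cost is a change of wording and some extra computation, with no new data. The drawback is wider bands and possibly no identifiable peak.
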